**Fig. 2 Fig2:**
[figure not shown]
Phase-2 flow diagram

### Outcomes

Phase 1: the main outcome will be the efficacy of the oral-hygiene procedures, evaluated by the total bacteria count, before and after the treatments (three groups and two time points). A secondary outcome that can be measured is the change in the pathogenic bacteria count that is related to VAP after the oral-hygiene procedures.

Phase 2: the main outcome will be the rate of VAP, evaluated by checking the medical cards, 5 days after the daily oral-hygiene procedures.

The detailed schedule for the study is presented in the SPIRIT figure (Fig. 3).

**Fig. 3 Fig3:**
[figure not shown]
Standard Protocol Items: Recommendations for Interventional Trials (SPIRIT) Figure: schedule of enrolment, interventions and assessments

### Data analysis plan

The studied parameters in this work will aim to follow a Gaussian (normal) distribution and they will be verified by the Shapiro-Wilk test. Where the data are not parametric, they will be transformed by using a logarithm or any other math transformation into normally distributed data. In this manner, parametric methods will be used in order to detect the differences among the groups. In order to show the actual distribution of the measured data, a graph based on the mean values and standard deviations will be used. For the data analyses, SPSS Statistics^TM^ Version 22 Software (IBM, Armonk, NY, USA) will be used. The statistical analyses will be realised by using analysis of variance (ANOVA): this will include the repeated measures as well as the within- and between-group interactions since three groups will be studied and each group will be measured before and after the oral-hygiene procedures. The frequencies of VAP occurrence will be measured in the two groups: (1) the most effective procedures found in phase 1 group and (2) the mechanical cleaning with filtered water group. The chi-square test will be used to verify the difference between the observed frequencies. The significance level for all of the tests will be *p* < 0.05. The results of this study will be published in an international journal.

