### Sample size calculation

First, a published paper using the same method of sample analyses (PCR + PMA pre-treatment) is to be used to determine the effect size (*Δ*). The largest and the smallest mean values (1.69 and 0.27, respectively), as well as the standard deviation (*σ* = 0.36) of the PCR quantification of living bacteria using PMA were taken from the Àlvarez article, 2013 [50]. The *n* value is to be the number of treatment groups, i.e., 3:$$ \varDelta =\frac{Largest- smallest}{{\left(\frac{\sigma }{\sqrt{n}}\right)}^2}=\frac{1.69-0.27}{{\left(\frac{0.36}{\sqrt{3}}\right)}^2}=32.8 $$

G*Power software (version 3.1.9.2, Dusseldorf, Germany) was used to calculate the sample size. Using the calculated effect size, *F* tests will be chosen for the repeated measures and for the within-between interactions. Three groups will be studied and each group will be measured before and after the oral-hygiene procedures (i.e. three groups and two measurements). The sample size was determined by setting a two-sided error at 5% and the test power at 95% of the test. According to the calculations, a sample of six patients per group will be necessary in order to detect the differences in oral hygiene in phase 1. When considering this result and the possibility of difficulties in the sample processing, phase 1 will be conducted with 10 patients per group.

The sample size calculation for phase 2 was based on the percentages of patients with VAP before and after the implementation of oral-dental care, as published by Garcia et al. [8]. Using G*Power software, when choosing the Exact Family Test and Fisher’s Exact Test as statistical tests (inequality, two independent groups) and by inserting the proportions of 0.086 and 0.041 [8], the sample size was found to be 52, i.e. 26 patients per group. It is important to highlight that at this phase, a 5-day protocol will be evaluated. Due to the condition of the patients, some of them may recover and the mechanical ventilation will be removed, while some may get worst or even die. Due to these potential dropout patients, a sample size of 70 patients (35 per group) will be used.

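### Phase 1's two-time-point repeated-measures ANOVA is a valid change-score test, but usually less precise than baseline-adjusted ANCOVA, and its analysis scale is left to the data

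*Protocol article*

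**What the plan says.** The Outcomes section makes the phase 1 main outcome the total bacteria count "before and after the treatments (three groups and two time points"). Interventions in phase 1 has the T0 swab taken before the randomised procedure and the T1 swab 30 minutes after it.

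The Data analysis plan states that the analysis will be "realised by using analysis of variance (ANOVA): this will include the repeated measures as well as the within- and between-group interactions". The Sample size calculation uses the same model: F "tests will be chosen for the repeated measures and for the within-between interactions". Neither section mentions a baseline covariate or gives a pre-post correlation.

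On the scale, the Data analysis plan says of normality that the parameters are such that "they will be verified by the Shapiro-Wilk test", and continues: "Where the data are not parametric, they will be transformed by using a logarithm or any other math transformation into normally distributed data". The logarithm is therefore the first-named option. It is used only if the normality check fails, and other transformations are equally allowed.

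Study design and Interventions in phase 2 carry the most effective phase 1 procedure forward into phase 2.

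**The concern.** Two choices are made less well than the design allows.

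- **Model.** The interaction test compares mean changes. It subtracts the whole baseline value from each patient's result, whatever the correlation between T0 and T1. When that correlation is modest, this adds baseline noise to the comparison. T0 precedes the randomised procedure, so it can serve as a covariate, and the data then determine how much of it to subtract.
- **Scale.** If the raw counts pass the normality check, the effect is an absolute difference in counts. If they fail and the log is used, it is a fold difference. If another transformation is used, it is something else. The meaning of the main phase 1 result is therefore settled only after the data are seen.

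Phase 1 exists to choose the procedure for phase 2, with 10 patients per group. A noisier contrast makes a wrong choice, or no clear separation, somewhat more likely.

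**Working it through.** **Inputs from the protocol article.** Three groups, two time points (Outcomes). Ten per group, N = 30; planning means 1.69 and 0.27; SD 0.36; two-sided 5% and 95% power (Sample size calculation).

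**Assumed, because the article gives no value.** The pre-post correlation ρ, the ratio of post to pre SD, and the effect sizes of 0.5, 1 and 2 SD used below.

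**1. The plan's own figures.** The stated effect size follows from the stated formula: (1.69 − 0.27) / (0.36/√3)² = 1.42 / 0.0432 = 32.87 (stated as 32.8). Taken as the effect size of the interaction F test, it gives over 99.9% power at a total of 4 patients, so the stated six per group is not reproduced. That is a separate matter, and nothing below depends on it. The planning difference in SD units is 1.42 / 0.36 = 3.94.

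**2. The interaction is a change-score test.** In a simulated data set of 3 × 10 patients, the group-by-time F was 1.4007 on 2 and 27 df. The one-way F on T1−T0 was also 1.4007. The identity is exact.

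**3. Variance with equal pre and post SD σ.** Change score: 2(1 − ρ)σ². ANCOVA: (1 − ρ²)σ². The large-sample ratio is (1 + ρ)/2. Estimating the slope multiplies the ANCOVA variance by 1 + 1/(N − 5) = 1 + 1/25 = 1.04.

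| ρ | (1+ρ)/2 | × 1.04 |
|---|---|---|
| 0 | 0.50 | 0.52 |
| 0.3 | 0.65 | 0.68 |
| 0.5 | 0.75 | 0.78 |
| 0.7 | 0.85 | 0.88 |
| 0.8 | 0.90 | 0.94 |
| 0.9 | 0.95 | 0.99 |
| 0.95 | 0.975 | 1.01 |

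Break-even: 1.04(1 + ρ)/2 = 1, so ρ = 2/1.04 − 1 = 0.92.

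**4. Unequal SDs.** Let k be post SD divided by pre SD. In units of the baseline variance, the change-score variance is 1 + k² − 2ρk and the ANCOVA variance is k²(1 − ρ²). The difference is (1 − ρk)², which is never negative and is zero at k = 1/ρ. For example, at ρ = 0.5 and k = 2 both variances equal 3, and after the 1.04 factor ANCOVA is 4% worse. The corresponding k is 1/0.3 = 3.3 at ρ = 0.3 and 1/0.7 = 1.4 at ρ = 0.7.

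**5. Power for one pairwise difference.** Noncentral t, 10 per group, equal SDs, 27 df (change) and 26 df (ANCOVA, slope cost included):

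| Difference | ρ | Change score | ANCOVA |
|---|---|---|---|
| 1 SD (assumed) | 0.3 | 45% | 60% |
| 1 SD (assumed) | 0.5 | 58% | 68% |
| 1 SD (assumed) | 0.7 | 80% (79.5) | 84% |
| 2 SD (assumed) | 0.3 | 95% | 99% |
| 3.94 SD (planning values) | 0 or more | about 100% | about 100% |

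**6. Choosing the best arm.** Simulation with one arm better by an assumed 0.5 SD and the other two equal. The best observed arm was the right one in 72% of runs by change score and 80% by ANCOVA at ρ = 0.3. The figures were 79% and 83% at ρ = 0.5, and 87% and 89% at ρ = 0.7.

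**7. Validity.** With no group difference, both tests rejected in about 5% of 20,000 simulated trials (4.9 to 5.1%) across ρ from 0 to 0.95.

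**The case against.** The strongest reply is that this is a preference for efficiency and not an error. The planned test holds its 5% level on a fixed scale, the model is named, and the sizing and analysis sections agree on it. An article may also leave covariate adjustment to a fuller plan. All of this stands except the last part: the article does name a model, so the choice can be improved.

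The second reply concerns size. The 1 SD difference behind the 45% to 60% gain is not in the protocol. At the protocol's own planning difference there is nothing to gain, and the correlation and SD ratio are unknown. This also stands, and it limits the claim.

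The third reply is that the logarithm is already named first, and that the trigger is a normality check and not the treatment effect. That is correct. A reader might infer that transformations will be tried one after another until one passes, that Shapiro-Wilk will be run within groups of 10, or that the reported p-value is distorted by a search. The text says none of these. It does not state whether the check is per group, pooled or on residuals, and no distortion has been calculated. What remains is narrower: the scale is not fixed before the data are seen, and the allowed list has no end.

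**Conclusion.** The point holds as an improvement that needs no new data, not as a flaw that invalidates phase 1. On a common scale with equal SDs, ANCOVA reduces the variance of the group contrasts by about 32%, 22% and 12% at assumed correlations of 0.3, 0.5 and 0.7. The reduction is about 6% at 0.8 and gone above about 0.92. It also disappears when the post-treatment SD exceeds the baseline SD by a factor near 1/ρ. Where ANCOVA loses, the loss at 10 per group is about 4% of variance at most.

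A reader might infer that phase 1 is underpowered because of this choice. The documents do not support that: at their own planning values either test has about 100% power. The gain matters only if the true difference is well below those values. The open scale is a separate weakness that does not depend on ρ, because it leaves the kind of effect being estimated undecided.

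**What to change.** In the Data analysis plan:

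- Name log10 bacterial count as the phase 1 analysis scale in advance, without a prior normality test, and delete the open choice of transformations.
- Make the primary phase 1 analysis an ANCOVA of log10 T1 on group with log10 T0 as covariate. Report the 2-df group test first, then the adjusted pairwise differences with 95% confidence intervals.
- Keep residual checks and a rank-based analysis as sensitivity analyses.

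Add a sentence to the Sample size calculation noting that sizing used the interaction F test while the analysis is the ANCOVA.

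The cost is one residual degree of freedom (27 to 26) and some wording, with no new data. Trial status says recruitment has not started, so the change can be made before any result is seen.

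### Phase 2 is sized with Fisher's exact test but analysed with an unspecified chi-square test; at the 1 to 3 VAP cases expected per arm, a borderline result would depend on the test or variant run

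*Protocol article*

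**What the plan says.** The main outcome of phase 2 is binary per patient (Outcomes): "Phase 2: the main outcome will be the rate of VAP, evaluated by checking the medical cards, 5 days after the daily oral-hygiene procedures".

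The Sample size calculation plans this comparison "when choosing the Exact Family Test and Fisher’s Exact Test as statistical tests (inequality, two independent groups"), and continues: "by inserting the proportions of 0.086 and 0.041 [8], the sample size was found to be 52, i.e. 26 patients per group". After an allowance for dropout: "Due to these potential dropout patients, a sample size of 70 patients (35 per group) will be used".

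The Data analysis plan names a different test: "The chi-square test will be used to verify the difference between the observed frequencies". It adds: "The significance level for all of the tests will be *p* < 0.05". It does not mention Fisher's test, does not say whether the chi-square is Pearson's uncorrected form or the continuity-corrected one, and gives no rule for small expected counts.

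**The concern.** The two sections name different tests for the same main comparison. With few events the difference matters, because the chi-square p-value rests on a large-sample approximation that is usually trusted only when every expected cell count is at least 5. If the counts are far below that, uncorrected chi-square, corrected chi-square and an exact test can fall on different sides of 0.05 for the same table. The phase 2 conclusion could then be settled by a choice of test or variant made after the data are seen, and the analysis would no longer match the basis of the sample size.

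**Working it through.** **Inputs.** VAP proportions 0.086 and 0.041, 26 per arm before and 35 per arm after the dropout allowance (Sample size calculation); significance at p < 0.05 (Data analysis plan). Tests are taken as two-sided. The protocol states two-sidedness only in the phase 1 paragraph, so for phase 2 this is an assumption.

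**The plan's own figure.** The stated 26 per arm is not reproduced. The usual formula, two-sided 5% and 80% power, gives

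n = [1.96·√(2 × 0.0635 × 0.9365) + 0.842·√(0.086 × 0.914 + 0.041 × 0.959)]² / (0.086 − 0.041)² = (0.676 + 0.289)² / 0.002025 ≈ 460 per arm.

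That is a separate matter. What follows takes 26 and 35 per arm as planned.

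**Expected VAP cases (n × rate).**

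| Per arm | At 8.6% | At 4.1% | Average, i.e. expected cell under no difference |
|---|---|---|---|
| 26 | 2.24 | 1.07 | 1.65 |
| 35 | 3.01 | 1.44 | 2.22 |

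With equal arms the expected event cell is half the total number of events, so it is below 5 whenever there are 9 events or fewer. At the average rate of 0.0635 that has probability 99.9% at 26 per arm and 98.7% at 35 per arm.

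**One table by hand: 4 v 0 at 35 per arm.**

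- Pearson: 70 × (4 × 35 − 31 × 0)² / (35 × 35 × 4 × 66) = 1,372,000 / 323,400 = 4.24, p = 0.039.
- Continuity-corrected: 70 × (140 − 35)² / 323,400 = 2.39, p = 0.122.
- Fisher: 2 × C(35,4) / C(70,4) = 2 × 52,360 / 916,895, p = 0.114.

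**Other tables at 35 per arm.**

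| Cases | Pearson | Fisher | Continuity-corrected |
|---|---|---|---|
| 3 v 1 | 0.303 | 0.614 | 0.607 |
| 4 v 0 | 0.039 | 0.114 | 0.122 |
| 5 v 0 | 0.020 | 0.054 | 0.063 |
| 6 v 1 | 0.046 | 0.106 | 0.111 |
| 7 v 1 | 0.024 | 0.055 | 0.060 |

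**All tables.** Weight each table (x, y) by its binomial probability under the assumed rates and add up those with p < 0.05.

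| Planning rates 8.6% and 4.1% | 26 per arm | 35 per arm |
|---|---|---|
| Pearson rejects | 7.1% | 11.3% |
| Fisher rejects | 0.9% | 2.1% |
| Continuity-corrected rejects | 0.8% | 2.1% |
| Pearson and Fisher disagree | 6.2% | 9.2% |

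In every disagreement it is Pearson that rejects.

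**Type I error, same method, equal rates in both arms, 35 per arm.** At 4.1%, 6.35% and 8.6%, Pearson's exact size is 2.7%, 4.7% and 5.6%; over all common rates its maximum is about 5.7%. Fisher's size at the same three rates is 0.1%, 0.5% and 1.0%.

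**Boschloo's test, 35 per arm.** Fisher's two-sided p is used as the statistic and its tail probability is maximised over the common rate. The p-values are 0.072 (4 v 0), 0.034 (5 v 0), 0.072 (6 v 1) and 0.038 (7 v 1). Rejection at the planning rates is 5.2%, with size held below 5%.

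**Sensitivity to the rates.** The Discussion cites VAP risks of 25% and about 19%. At 35 per arm these give 35 × 0.25 = 8.75 and 35 × 0.19 = 6.65 expected cases, and Pearson and Fisher disagree in 3.5% of trials.

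**The case against.** The strongest reply is that the named chi-square test does little harm. If it is uncorrected Pearson, its exact size is near or below 5% despite the small counts; if it is continuity-corrected, it rejects exactly as often as Fisher at 35 per arm. Both points stand. They show that each variant is defensible as a test, but not that the plan has chosen one: the two variants disagree on the four tables above.

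A reader might infer that about four in five Pearson-significant results (9.2 of 11.3 points) would be false. The documents do not support that. The ratio treats Fisher's verdict as the truth, whereas Fisher's size here is only 0.1% to 1.0%, so most of the gap is Fisher's conservatism. It also assumes the uncorrected variant, which the plan does not state.

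Nor does significance depend on the test in general. The tests agree in about 91% of trials at the planning rates, and at about the expected counts (3 v 1) none is significant.

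The events might also be more frequent than planned. The phase 2 interventions section accepts a pneumonia diagnosis on any one of several criteria, and the Discussion cites higher risks. That would reduce the problem without removing it, as the 3.5% shows.

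Finally, the sample size is the larger weakness. True, but it is a separate point, and few events make the choice of test matter more.

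**Conclusion.** The point holds as an inconsistency with a limited but real consequence. The sections name different tests for the phase 2 main outcome, the chi-square variant is open, and at the planning rates the usual condition for the approximation almost certainly fails. For the tables most likely to look positive, the verdict at 0.05 is then not determined by the plan. The size is disagreement in about 9% of trials at 35 per arm and the planning rates, and about 3.5% at 25% and 19%. These figures assume two-sided tests, 35 evaluable patients per arm, and uncorrected Pearson as one side of the comparison.

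Inflated type I error is not part of the finding. Neither is the lack of a confidence interval, a detail that an article may leave to the full protocol or analysis plan.

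**What to change.** Before recruitment, which the Trial status section says has not started, name one two-sided exact test for the VAP comparison in both the Sample size calculation and the Data analysis plan.

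- **Boschloo's test** is preferable: it holds 5% and rejects in about 5% of trials at the planning rates with 35 per arm, against about 2% for Fisher. The sizing paragraph would then also have to name it, and its availability in the chosen software should be checked.
- **Fisher's test** needs only the analysis sentence changed, since the sizing already uses it, but it is very conservative here.

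The cost is about one sentence in each section. The downside of either is a lower rejection rate than uncorrected Pearson (11%). Reporting the risk difference with a 95% confidence interval is a useful option, not a requirement of this point. No choice of test repairs the phase 2 sample size: rejection at the planning rates is at most about 11% with any of them.

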## Discussion

Some studies have suggested that inefficient oral hygiene and VAP are related [6, 8, 55–58]. Hua et al. recently concluded in a systematic review that oral hygiene reduces the risk of developing VAP from 25% to about 19%. Nonetheless, no differences in the outcomes of mortality, the duration of the mechanical ventilations, or the duration of ICU stay were detected [59]. This protocol will aim to specifically verify the efficacy of PDT in the context of an ICU, when considering that a more effective oral-hygiene protocol can reduce VAP incidence. This can help in a patient’s recovery, reducing their ICU stay, together with the treatment costs to the Brazilian public health system. Besides, it is known that critically ill patients, such as ICU inpatients, present a different oral microbiome, mostly composed of Gram-negative bacteria and *Staphylococcus aureus*, being distinct from healthy individuals, who present higher levels of Gram-positive bacteria such as *Streptococcus viridans* [60, 61].

Chlorhexidine has been considered to be the ‘gold standard’ for oral hygiene in an ICU. However, it has also been associated with bacterial resistance. Due to the known PDT effects against different microorganisms and the absence of a microorganism resistance, this appears to be an interesting possibility. Some studies have shown that an MB vehicle can affect the efficacy of PDT [45, 46, 49]. Due to these facts, the study design will include the treatment that is considered to be the gold standard, together with PDT comprising two different vehicles for MB.

The Hospital Assembly of Mandaqui is a public hospital in the city of São Paulo, Brazil. The ICU receives some adult patients suffering from polytrauma. However, most of the patients are older people and are edentulous individuals. Due to the known differences between oral microbiota and edentulous and *dentate* individuals [4, 62], the panorama of inpatients in the hospital where this study is going to be conducted will only include those edentulous individuals in this protocol. Since different pathogens can co-exist in the same patient, the use of specific selective media to grow and count colonies would be expensive and time consuming. Therefore, our proposal is to perform the quantification by PCR when using a universal (16S) primer which can identify the total bacteria count. However, bacterial quantification by PCR can be puzzling, since the DNA of both live and dead bacteria would be measured together, generating conflicting results [63]. Bacterial quantification by PCR when using PMA achieves the selective detection of living bacteria by an easier method and is an innovation in terms of the analysis of patient samples in phase 1 of this study. PMA can be used as a viability marker as it is a chemical that crosses the dead cell membrane and when it is exposed to light, it intercalates the DNA strands, preventing their amplification. PMA allows for good results for different bacterial species in different types of samples [50, 64–68].

When considering microorganism resistance to many different antimicrobials [69], PDT appears to be an interesting tool, since it can be considered to be effective, independent of microorganism resistance. In addition, by using a low-cost photosensitiser and an illumination device, it becomes attractive for use in the Brazilian public health system. In this sense, MB is a low-cost photosensitiser and it has been widely studied in order to reduce pathogenic microorganisms in oral microbiota [16, 70–72]. However, this is the first trial to evaluate MB in a mouthwash formula that can increase its effectiveness due to the control of MB aggregation.

